#### Data collection

The NCQ will be distributed to patients in month 0 and 12 in all practices (Table 1). The participating general practices will be provided with a selection algorithm for identification of 100 eligible patients from the EMR. Eligibility criteria are: aged 65 or older, registered at the participating general practice, able to speak Dutch or English, community living, no severe cognitive impairment, and at least 1 GP consultation in the past 12 months. Eligible patients will receive a postal invitation for participation together with the questionnaire.

Digital surveys will be distributed to all GPs and practice assistants using Survalyzer at baseline (month 0) and during follow-up at 3, 6, 9, 12, 15 and 18 months. The baseline survey will address barriers and facilitators for implementation related to the practice organisation, structure and working methods. This survey will contain the same questions for all practices. The other surveys will prospectively measure the implementation, acceptability and feasibility, barriers and facilitators of the intervention during the trial. Because the intervention will be tailor-made per practice, each practice will receive surveys containing questions specifically formulated for that practice to ensure optimal data collection and ability to register unexpected events [48].

Two semi-structured telephone surveys will be held with coordinating GPs of all practices within one month and three months after the introduction of the TOOL-kit in that practice. In interview one, the fidelity, acceptability and other barriers for implementation of the TOOL-kit application will be adressed. Interview two will assess the practice improvement plan for personal continuity on the same parameters as interview one. In month 18, a concluding group interview will be held by videoconference per practice with all GPs and practice assistants to conclude the process evaluation.

The interviews will be conducted by a trained interviewer, voice recorded and transcribed verbatim afterwards.

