## Methods/design

The study will consist of five phases where the intervention will first be developed (phase 0, I and II) and subsequently evaluated in a randomised controlled trial (phase III) (Fig. 1). In the last phase, implementation will be assessed (phase IV). The study follows the Medical Research Council (MRC) framework for development and evaluation of complex interventions [48, 49].

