#### Randomisation and blinding

Practices will be randomised to a wedge using computer-generated random numbers in Microsoft Excel 2016 by a researcher from our group. General practices randomised to wedge 1 will start with the intervention immediately after baseline measurement. Practices of wedge 2 will start in the control condition, providing 3 months of usual care before receiving the intervention. Practices of wedge 3 will start in the control condition, providing usual care for 6 months before start of intervention.

Researchers will be blinded to group assignment during data analysis where possible. Due to the study design and nature of the intervention, researchers, GPs and practice assistants cannot be blinded to group assignment.

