#### Sample size

The sample size calculation was based on our primary outcome measure (the NCQ). For both NCQ distribution cycles in month 0 and month 12, we will approach 100 patients per practice. We expect at least 35 patients per practice to participate, resulting in a total of 1050 patients in each cycle. When the mean NCQ score is compared between cycles using a mixed linear model with a random effect for practice and two-sided testing at a significance level of 5%, the expected sample size allows detection of all standardized effect sizes of 0.12 and larger with at least 80% power irrespective of the intra-cluster correlation coefficient. The standardized effect size is defined as the difference in means divided by the total standard deviation incorporating both the between- and within-practice variation.

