#### Trial (phase III)

Descriptive statistics will be used to summarize population characteristics. For the primary analysis, the mean NCQ score at baseline and at 12 months follow-up will be compared using a linear mixed model with a random effect for practice and a fixed effect for time point. To analyse if differences depend on longer exposure to the TOOL-kit, the main effect of wedge number and the two-way interaction between wedge number and time point will be determined.

Secondary outcomes measures from the surveys will be compared before and after the intervention and between measurements on different time points using mixed linear models or generalized estimating equations depending on the type of outcome measure. This accounts for clustering of participants within the practices. For outcomes that are collected in more than two periods, the length of exposure to the TOOL-kit main determinant will be considered using the control condition as a reference. A two-sided significance level of 5% will be used for all analyses.

The semi-structured telephone interviews will be analysed according to the framework method described in the *focus groups* section.

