Phase III and IV of the study will probably take place during the current SARS-CoV-2 (coronavirus) pandemic. Because especially complex interventions interact with the context they are performed in, [73] it is likely that the effect of the intervention will be affected by the coronavirus pandemic. We aim to mitigate this effect by dedicating part of the interviews and surveys in our process evaluation to the influence of the coronavirus on general practice. Additional reminders will be sent to reduce non-response and practices will be contacted periodically to assess trial feasibility within that practice and to tailor design adaptions when necessary and where possible.

All phases of the study will focus on personal continuity in Dutch general practice. Although this increases the relevance of the study results for Dutch clinical practice and healthcare policies, additional translational steps may be required to ensure its relevance in other countries.

In summary, the overall aim of this study is to develop and evaluate a complex intervention for improving personal continuity: the TOOL-kit. We will do this by performing a literature study (phase 0), a survey, focus groups and a Delphi study (phase I) followed by a pilot (phase II) and a cluster randomised stepped wedge pragmatic trial (phase III). We will use the results of phase III to define the conditions for further implementation of the TOOL-kit (phase IV).

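### The primary NCQ comparison is an uncontrolled before-after contrast: every practice is unexposed at month 0 and exposed at month 12, so an exposed-versus-unexposed effect cannot be separated from calendar time

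*Protocol article*

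**What the plan says.** **Design label.** Methods/design says the intervention will be "subsequently evaluated in a randomised controlled trial (phase III"). The opening of Phase III calls this a stepped-wedge, cluster randomised pragmatic trial.

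**Roll-out** (Randomisation and blinding).
- Wedge 1: "General practices randomised to wedge 1 will start with the intervention immediately after baseline measurement".
- Wedge 2 starts in the control condition, "providing 3 months of usual care before receiving the intervention".
- Wedge 3: "Practices of wedge 3 will start in the control condition, providing usual care for 6 months before start of intervention".

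**Primary outcome dates.** Data collection: "The NCQ will be distributed to patients in month 0 and 12 in all practices". Sample size agrees: "For both NCQ distribution cycles in month 0 and month 12, we will approach 100 patients per practice".

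**Primary analysis** (Trial, phase III): "the mean NCQ score at baseline and at 12 months follow-up will be compared", using a linear mixed model with a random practice effect and a fixed time-point effect. A wedge main effect and a wedge-by-time interaction are added to see whether differences depend on longer exposure.

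**Power** (Sample size): 35 responders in each of 30 practices, 1050 per round, are said to detect 0.12 SD with at least 80% power whatever the ICC.

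**Context.** The Discussion expects Phase III to run during the pandemic and states that "it is likely that the effect of the intervention will be affected by the coronavirus pandemic". The measures listed are process-evaluation questions, extra reminders, periodic contact with practices, and tailored design adaptations.

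**The concern.** A stepped wedge yields a randomised estimate because, at some measurement times, some clusters have crossed over and others have not. Here the staggered start creates such times between month 0 and month 6, but no NCQ is collected then. The usual-care months of wedges 2 and 3 contribute no primary-outcome data.

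The change from month 0 to month 12 would then be read as the TOOL-kit effect, although it also contains whatever else altered older patients' ratings of continuity over that year. None of the measures in the Discussion separates the two. A reader who sees the randomised stepped-wedge label would credit the primary result with a protection against time trends that it does not have.

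**Working it through.** **1. Exposure at each NCQ round** (start months from Randomisation and blinding)

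| Wedge | TOOL-kit starts | Month 0 | Month 12 |
|---|---|---|---|
| 1 | just after month 0 | unexposed | 12 − 0 = 12 months |
| 2 | month 3 | unexposed | 12 − 3 = 9 months |
| 3 | month 6 | unexposed | 12 − 6 = 6 months |

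An exposed/unexposed indicator equals the month-12 indicator in every practice. A model with two period means and that indicator has three parameters, but its information matrix has rank 2. No sample size repairs this.

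**2. The plan's own power figure.** Total SD is 1, with 1050 responders per round. I assume that responses in the two rounds are independent given practice and that there is no practice-by-time variance. The practice effect cancels, so SE = √(2(1 − ICC)/1050), and the detectable difference is (1.960 + 0.842) × SE.
- ICC 0: SE = 0.0436; detectable difference 0.122; power at 0.12 SD 78.5%.
- ICC 0.05: detectable difference 0.119; power 80.5%.
- ICC 0.10: detectable difference 0.116; power 82.6%.

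The stated 0.12 SD with 80% power is thus reproduced to rounding, and it is reproduced as a before-after contrast between two rounds.

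**3. Sensitivity to drift.** Let the true effect be zero and the secular shift be d. Rejection probability = Φ(d/SE − 1.96) + Φ(−d/SE − 1.96), with SE = 0.0436. The values of d are assumed; the protocol gives none.
- d = 0.05: d/SE = 1.146, giving 21%.
- d = 0.10: d/SE = 2.291, giving 63%.

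**4. The randomised contrast that remains.** This is the change in wedge 1 minus the change in wedge 3 (12 versus 6 months of exposure), assuming 10 practices and so 350 responders per wedge per round. With cluster autocorrelation c, variance = 4[(1 − ICC)/350 + ICC(1 − c)/10].
- ICC 0: SE = √(4/350) = 0.107; detectable difference 0.30 SD.
- ICC 0.10, c = 1: SE = √(4 × 0.9/350) = 0.101; detectable difference 0.28 SD.
- ICC 0.10, c = 0.8: SE = √(4 × (0.00257 + 0.00200)) = 0.135; detectable difference 0.38 SD.

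An effect that was immediate and constant would make this contrast zero, however large the effect.

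**5. Adding rounds at months 3 and 6.** Each round is taken just before that month's crossover, and the 200 mailings per practice are kept. Expected responders are 2 × 35/4 = 17.5 per practice per round. The model has four period means and an exposure indicator, fitted by generalised least squares to practice-period means. It has rank 5 of 5, so the effect is estimable. Detectable differences for ICC 0.02 to 0.10:

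| Schedule | c = 1 | c = 0.8 |
|---|---|---|
| Months 0 and 12, before-after | 0.116–0.121 | 0.129–0.155 |
| Months 0, 3, 6, 12, same mailings | 0.206–0.213 | 0.209–0.246 |

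The second row assumes an immediate, constant effect. If the effect builds linearly to full size over 6 months, this constant-effect model recovers about 56–60% of it. If it builds over 12 months, the model recovers about 16–24% of the month-12 effect.

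**The case against.** **The protocol does use the wedges.** The wedge-by-time interaction is prespecified and randomised. That stands. A reader might infer that randomisation is wholly unused, or that the two-round schedule permits no estimate under any model. Neither follows. Non-estimability holds for an exposed/unexposed term; with exposure coded in months, the two rounds give a full-rank model, though an imprecise one (a detectable 12-month effect of about 0.42–0.69 SD for ICC 0–0.10 and c = 0.8–1). It yields an effect against no exposure only by assuming the shape of the response to duration.

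**The before-after comparison is openly described.** Sample size and the analysis section say that two time points are compared and do not call that contrast randomised. This also stands: the conflict is with the design label in Methods/design and at the start of Phase III.

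**The pandemic statement is not evidence of drift.** A reader might take "it is likely that the effect of the intervention will be affected by the coronavirus pandemic" as an admission that scores will shift. It speaks of the intervention's effect being modified. A secular shift in NCQ is an inference, and the drift sizes above show sensitivity only. Nor does the Discussion rely on process questions alone; it also lists reminders, practice contacts and adaptations.

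**Staged roll-out was chosen for ethical and logistical reasons.** True, but those reasons concern when practices start, not when the NCQ is sent.

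**More rounds may not be better.** This carries weight. The early rounds see only about three months of exposure, and the power loss is considerable. The four-round schedule is therefore an option, not the required remedy.

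**Conclusion.** The point holds, limited to the primary NCQ contrast. As fixed in the protocol, that contrast is an uncontrolled before-after comparison in which an exposed-versus-unexposed effect is inseparable from calendar time. This follows from the stated dates and does not depend on any ICC or sample size. A later analysis plan could not repair it, because no NCQ data would exist from a time when exposed and unexposed practices coexist. The schedule table is not readable in the text at hand, but Sample size, Data collection and the analysis section agree on two rounds.

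The only randomised NCQ result concerns duration of exposure. Its detectable difference is about 0.28–0.30 SD without practice-by-time variance and up to about 0.38 SD at ICC 0.10 with autocorrelation 0.8. These figures rest on 10 practices per wedge, which is assumed. It should be corrected before the result is presented as that of a randomised trial.

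**What to change.** **Needed in any case.**
- In Methods/design, the opening of Phase III, Sample size and Trial (phase III), state that the primary result is a before-after comparison confounded with calendar time, and that the 0.12 SD / 80% figure applies to that contrast.
- Do not attribute the change to the TOOL-kit on the strength of randomisation.
- Report the wedge-by-time contrast as the only randomised NCQ result, fitted as a one-degree-of-freedom term in months of exposure with a common month-0 mean.

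This costs wording and one respecified model term, and no new data.

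**Option, if the dates can still move.** Also collect the NCQ at months 3 and 6, just before wedges 2 and 3 cross over. Fit period and exposure effects with random practice and practice-by-period terms, and let the effect depend on time since introduction. The costs should be stated:
- With the same 200 mailings per practice, the detectable difference is about 0.21–0.25 SD under an immediate constant effect, against about 0.12–0.155 SD for the before-after contrast over the same ICC and autocorrelation range. A time-since-introduction model would need its own power calculation.
- There are two further postal rounds, each with a patient selection from the medical record in every practice.
- A constant-effect model would understate a gradual effect to the extent shown in step 5 of the working.

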#### Intervention

The TOOL-kit will be introduced in all participating practices during the course of the study. After receiving the TOOL-kit, practices will be instructed to use it to optimise personal continuity for their older patients. Because the TOOL-kit is introduced on a practice level, all employees and all patients of a practice will be exposed to the intervention. Its introduction is the complex intervention of the study.

The TOOL-kit will consist of multiple components defined in phase 0, I and II. As complex interventions may work best when adapted to local circumstances [48], the TOOL-kit will contain both components which are obligatory and identical for all practices and optional components tailored to the local circumstances of a practice. The components will include professional-oriented strategies (e.g. educational materials, audits and feedback), patient-oriented strategies (e.g. decision aids, arrangements for (direct) contact with healthcare providers) and organisation-oriented strategies (e.g. arrangements for follow-up of patients, revision of professional roles) [58].

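### If the one-consultation criterion is reapplied at month 12, its look-back is the trial year, and the primary model has no patient covariates to absorb a resulting change in case mix

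*Protocol article*

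**What the plan says.** All references are to the protocol article.

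- **Timing** (Data collection): "The NCQ will be distributed to patients in month 0 and 12 in all practices".
- **Selection** (Data collection): "The participating general practices will be provided with a selection algorithm for identification of 100 eligible patients from the EMR". Eligibility has six parts: age 65 or over, registration with the practice, language, living in the community, no severe cognitive impairment, "and at least 1 GP consultation in the past 12 months".
- **Numbers** (Sample size): "For both NCQ distribution cycles in month 0 and month 12, we will approach 100 patients per practice". Then: "We expect at least 35 patients per practice to participate, resulting in a total of 1050 patients in each cycle". The target is a standardised difference of 0.12 with at least 80% power, whatever the intra-cluster correlation (ICC).
- **Start of the intervention** (Randomisation and blinding): directly after baseline in wedge 1, after 3 months in wedge 2, after 6 months in wedge 3.
- **Content of the intervention** (Intervention): the examples of organisational strategies are "arrangements for follow-up of patients, revision of professional roles". Arrangements for direct contact with providers are an example of a patient-oriented strategy.
- **Primary analysis** (Analysis, Trial (phase III)): month 0 is compared with month 12 in a linear mixed model with a random effect for practice and a fixed effect for time point. Wedge and its interaction with time point are then examined. No patient-level term is named.

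The text says neither that the algorithm is rerun at month 12 nor that the month-0 patients are approached again.

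**The concern.** At month 0 the 12-month look-back lies wholly before the trial. Reapplied at month 12, the same rule looks back over the trial year, most of which is exposed to the TOOL-kit. Eligibility is then measured after randomisation and can respond to the intervention. Changes in follow-up, direct contact or professional roles could bring in some older patients who would otherwise not have consulted a GP that year, or take some out.

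The primary contrast is a before-after comparison in practices that are all exposed by month 12. There is no concurrent control, so a change in the kind of patient sampled cannot be told apart from a change in continuity. The wedge-by-time interaction does use the randomisation, but it is not protected either, because the exposed share of the look-back differs by wedge. The target effect is small, so a modest change in mix could matter.

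**Working it through.** **1. Fresh sample or cohort?** Four features point to separate samples: 100 patients approached and 35 expected per practice in each cycle, no mention of patient attrition, no patient effect in the model, and a power statement that fits independent samples (step 2). This is an inference.

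**2. The plan's own figure.** Inputs from Sample size: 30 × 35 = 1050 per cycle, difference 0.12 total SD, two-sided 5%. With two independent samples from the same practices, the practice effect cancels:

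SE = √[2(1 − ICC)/1050]; at ICC = 0 (the worst case here), SE = √(2/1050) = 0.0436.

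Power = Φ(0.12/0.0436 − 1.96) = 0.785 at ICC 0, 0.805 at ICC 0.05 and 0.826 at ICC 0.10. The smallest difference detectable with 80% power at ICC 0 is (1.960 + 0.842) × 0.0436 = 0.122. The stated figure is reproduced to rounding.

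**3. Exposure within the look-back.**

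| Wedge | Exposed months of the month-0 window | Exposed months of the month-12 window |
|---|---|---|
| 1 | 0 of 12 | 12 of 12 |
| 2 | 0 of 12 | 9 of 12 |
| 3 | 0 of 12 | 6 of 12 |

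With equal wedges this is 27 of 36 wedge-months, or 75%.

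**4. What a change in mix would do.** Let q be the share of month-12 respondents who are present only because the eligible pool changed. Let D be the difference in mean NCQ, in SD, between them and the patients they replace. The month-12 mean shifts by q × D. With no true effect, the two-sided rejection rate is 1 − Φ(1.96 − qD/SE) + Φ(−1.96 − qD/SE), with SE = 0.0436. The documents give neither q nor D, so **both are assumptions**:

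| q | D | Shift (SD) | Share of 0.12 | False positives |
|---|---|---|---|---|
| 5% | 0.2 | 0.01 | 8% | 5.6% |
| 10% | 0.3 | 0.03 | 25% | 10.6% |
| 10% | 0.5 | 0.05 | 42% | 20.9% |
| 20% | 0.5 | 0.10 | 83% | 63.0% |

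A shift equal to the full target needs q = 0.12/D: 60% at D = 0.2, 40% at 0.3, 24% at 0.5 and 15% at 0.8.

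**The case against.** Most of the case on the other side stands, and it limits the point.

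- **A reader might infer that month-12 patients are definitely newly selected.** The documents do not say so. If the month-0 patients are followed as a cohort, the look-back precedes the intervention and the problem does not arise. The schedule in Table 1 might settle this, but it was not readable in the copy used here.
- **A reader might infer that the intervention decides who is compared.** That is too strong. One consultation in a year is a low threshold and one of six criteria. The contact and follow-up components are only examples, since the content was still to be defined in phases 0 to II. Nothing in the documents shows that the TOOL-kit moves patients aged 65 or over between no consultation and one. The most that can be said is that it can influence eligibility.
- **A reader might infer that the pandemic separates the two windows.** The Discussion expects phase III to fall within the pandemic, and the baseline look-back may do so too. A difference is possible but not shown.
- **A reader might infer that practices hand-pick patients, or that non-response causes the bias.** Practices use a supplied algorithm, and no discretionary choice is described. The expected response of 35 in 100 is the same in both cycles and creates no before-after difference by itself.
- **Covariates may be left to an analysis plan.** That plan is not shown and may contain them. The article does, however, state the terms of the primary model, and as stated nothing in it absorbs a change in patient mix.

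What remains is the overlap of the look-back with the trial year under the likelier reading, and an uncontrolled contrast without patient terms.

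**Conclusion.** The point holds conditionally. If the consultation criterion is reapplied at month 12, eligibility depends on a period in which the intervention is active for 6 to 12 of 12 months, and the stated primary model passes any change in case mix straight into the estimated effect. The documents fix neither the size nor the direction of the bias. At the low end of the assumed inputs it is negligible; at the high end it reaches 0.10 SD, still below the 0.12 SD target but enough to make a false positive more likely than not. These rates rest on assumed q and D, independent samples and ICC 0. They show sensitivity and do not forecast the bias. The correction is cheap and concerns the primary outcome, so it is worth making.

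**What to change.** 1. In Analysis, Trial (phase III): add age, sex and the number of GP consultations before month 0 (from the EMR) as fixed effects in the primary NCQ model. None of these can be changed by the intervention. They reduce case-mix bias but cannot be expected to remove all of it.
2. As a sensitivity analysis: restrict month-12 respondents to those who also met the consultation criterion at month 0. This removes patients who became eligible only during the trial year. It does not restore patients who dropped out of eligibility.
3. In Data collection: state whether the month-12 patients are a fresh sample or the month-0 patients approached again. If it is a cohort, the look-back problem falls away.

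Replacing the rolling criterion with a list frozen at month 0 should not be required. It would anchor eligibility before the intervention, but month-12 raters would then be drawn from a list a year older and might have had no GP contact in the intervention year. Age and recency of contact would then differ between cycles, so one difference in mix would be traded for another.

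**Cost:** a small EMR extract per sampled patient, slightly more analysis and one clarifying sentence.
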